### Eligibility

To be eligible for this randomized controlled study, subjects must fulfill all of the following inclusion criteria: (1) aged 60 years or older, (2) identified as food insecure in the recruitment [21], (3) able and willing to give written informed consent and phone number contact and comply with other requirements of the study protocol, (4) Portuguese speaker or able to understand Portuguese, (5) noninstitutionalized and living in a private household in Portugal, (6) have electricity at home, and (7) have cable TV with box at home. The exclusion criteria are as follows: (1) inability to comply with study protocol (hearing/visual loss, cognitive impairment, etc); (2) absolute contraindication to exercise; (3) have cable TV operated by other companies than MEO, Vodafone, or NOS; and (4) have a household member involved in this study.

### Description of the Intervention

Our intervention program is based on a cognitive behavioral strategy for promoting lifestyle behavior changes, combining sets of different strategies that will be important to the learning process as well as to behavioral changes.

This tool was developed based on the transtheoretical model [22] that conceptualizes the process of intentional behavior change in 5 stages, from precontemplation to maintenance. This intervention program accompanies the participants through all these phases. At T0 clinical appointments, doctors, nutritionists, physiotherapists, and nurses lead the participant through the stages of precontemplation and contemplation. In the preparation and action phases—when the subject intends to change behaviors and in fact does change them—the intervention program offers them all the cognitive and behavioral tools to achieve the changes. In addition, the intervention promotes helping relationships, since participants have at their disposal the telephone number and the possibility to contact the team as regularly and as often as they wish. The program also considers the phases of maintenance and prevention of relapse in the T1 clinical appointment and 3 months after the program.

The contents of the intervention program using a TV app were developed closely regarding Kolb’s experiential learning model [23,24]: videos on physical exercise and recipes (reflective and active experimentation); videos with tips on nutrition and healthy lifestyles (abstract conceptualization); queries; reminders; and the option to contact the medical doctor, nutritionist, nurse, and physiotherapist.

We designed an interventional program using an interactive TV app to improve dietary habits and physical activity levels among elderly populations with food insecurity. Of the several ICTs available, we have chosen the TV app because the majority of elderly people with food insecurity watch TV [25]. Unpublished data from our group have shown that TV is the most important source of health information for this group.

Our intervention consists of a 12-week home-based intervention with a comprehensive program on healthy eating and physical activity, specially designed for the elderly. This program is an innovative interactive TV app for healthy lifestyle promotion and was designed taking into account (1) the need to educate elderly people about the importance of a healthy diet and exercise, (2) the need to explain that low household income is not a barrier to healthy lifestyles and it is possible to have a healthy diet and physical activity habits at low cost, and (3) the importance of motivating individuals to eat healthier and engage in more physical activity in order to reduce noncommunicable diseases. This interventional program is composed of 3 parts: nutrition and diet tips for healthy eating, low-cost healthy recipes, and physical exercise programs. The nutrition tips content was adapted for people who have economic difficulties in accessing food. In fact, all of the contents were based on a book published by the Portuguese Directorate-General of Health, developed with the main aim of improving dietary habits of low-income people. For example, we promote the consumption of eggs as one of the most economical choices among the good sources of protein, we promote the consumption of vegetarian sources of protein (pulses), and we promote the consumption of seasonal fruit and vegetables because fresh produce often costs less and is a nutritious option. The recipes were developed in order to show how to prepare healthy, tasty, and low-cost recipes. Finally, the physical activity video shows that is possible to do some physical activity at home without spending money.

All of the contents were disseminated on a dedicated channel through a TV app in a video format. As part of the motivation approach of our intervention program, brief reminders on health behaviors will also be diffused weekly through the TV app. These brief reminders will be powerful in recalling and stimulating study participants to adhere, encouraging lifestyle changes. Moreover, frequent contacts with participants are a relevant aspect of successful behavior change intervention programs [26], and follow-up monitoring is included in our program in order to monitor changes in specific behaviors and knowledge during the intervention period. With that purpose, short questionnaires will be delivered weekly through the TV. Thus, the interactive app will be used to collect data (short questionnaires) to evaluate the program compliance and learning. With these short questionnaires we aim to capture lifestyle changes and evaluate the learning along the intervention period. These questionnaires can easily be answered by pushing TV remote control buttons.

This 12-week TV-delivered program is composed by thematic weeks, and all of the contents (“nutrition and diet tips for healthy eating” videos, “healthy recipes” videos, brief reminders, and short questionnaires) developed for each week were specially designed to take into account the thematic week (Table 1).

**Table 1 table1:** Theme of each week of the interventional TV app on healthy eating and physical activity.

Week	Theme	Content
1	**Vegetable week**	
		Health benefits of vegetable consumption
		Recommendations for vegetable intake
		How to increase the daily intake of vegetables
2	**Water week**	
		Water, hydration, and health
		Recommendations for water intake
		Food resources that contain water
3	**Milk week**	
		Health benefits of consumption of milk and other dairy products
		Recommendations for milk intake
4	**Olive oil week**	
		Olive oil as a healthy cooking oil option
		Adequate amounts for using olive oil for food preparation and cooking
5	**Fruit week**	
		Health benefits of fruit consumption
		Recommendations for fruit intake
6	**Salt week**	
		Health risks of salt intake
		Recommendations for salt intake
		Foods with high and low salt content
		Strategies to reduce salt intake
7	**Meat, seafood, and eggs week**	
		Importance of consuming adequate amounts of meat, seafood, and eggs
		Adequate portions of meat, seafood, and eggs
		Healthier food options within the different foods of this group
8	**Vegetable soup week**	
		Health benefits of vegetable soup consumption
		Standard recipe for a healthy vegetable soup
9	**Vegetable and fruit week**	
		Health benefits of vegetable and fruit consumption
		Recommendations for vegetable and fruit intake
		Meeting vegetable and fruit intake recommendations
		How choose the low cost options for these foods
10	**Healthy cooking week**	
		How to cook healthy food
11	**Sugar week**	
		Health risks of sugar intake
		Recommendations for sugar intake
		Foods with high and low sugar content
12	**Pulses week**	
		Health benefits of pulses consumption
		Recommendations for pulses intake
		How to include pulses in your diet daily intake

The themes for each week and consequently the contents of each video on nutrition and diet tips for healthy eating were chosen considering the main concerns on diet, in particular the main risk factors for noncommunicable diseases that are associated with unhealthy diets and the nutritional requirements for elderly people [27-29]. The low-cost healthy recipes are chef-created recipes and were specifically developed for our program by a popular Portuguese TV chef with a consulting nutritionist. The physical activity program was developed by physical exercise experts with the main goal of encouraging at least 30 minutes of physical exercise at home 3 times per week [30].

The delivery of these contents through the TV app will be scheduled for specific days of each week in order to develop a routine and constant program over the intervention period. Each day, 1 program will be available (Table 2). The TV app was developed by an external company, and the main TV cable operators agreed to disseminate this app.

**Table 2 table2:** Weekly schedule of the intervention delivery.

Weekday	Hour	Program delivery
Monday	2:00 PM	Nutrition and diet tips for healthy eating
Tuesday	12:00 PM	Healthy and low-cost recipes
Wednesday	9:00 AM	Physical exercise program
Thursday	2:00 PM	Brief reminder
Friday	Not fixed	Questionnaire
Saturday	Not fixed	Questionnaire
Sunday	—	—

During the development of the TV app, a focus group was conducted by a trained psychologist using a semistructured interview to assess the concept of the TV app, its usability, the adherence intention, and the expected impact on behavior modification. To this end, 11 subjects (6 women and 5 men) with similar characteristics to the study population were enrolled. In terms of the concept of a “TV-based intervention on healthy lifestyles promotion in the reduction of food insecurity in elderly subjects,” the members of the focus group generated immediate, very positive, and homogeneous reactions in respondents. The unsolicited comments were many and denoted a strong reception of the concept by all respondents. On the other hand, there was a clear projective identification with the tested app, since it addresses some of the issues that most concern this group: healthy lifestyles, diet, nutrition, and exercise.

Regarding the sense of usability, participants pointed out that the TV is a familiar device and, for that reason, considered the TV app easy to use. On the other hand, little sensitivity in the fingers to handle the remote control and the lack of vision to distinguish a few keys and buttons were stated as likely barriers to its use. Concerning the adherence intention, all respondents were willing to have this app in their homes and report feeling motivated to use it because it is a targeted tool for them.

The TV app seemed to have the potential to generate a positive impact on changing behaviors of seniors. This focus group reported general satisfaction and motivation. Nevertheless, the impact assessment will only be possible at a later stage of use. By using this cognitive behavioral strategy, we reinforce elderly learning and behavioral modifications for promoting lifestyle behavior changes.

After the TV app is completed, a pilot study will be performed in order to test (1) the TV app diffusion conditions by the TV cable operators, (2) TV app user experience, (3) subjects’ adherence to the TV app, and (4) subjects’ behavioral changes through qualitative analysis. For this study a small sample (n=30) of elderly people with and without food insecurity will be recruited (Figure 2).

**Figure 2 figure2:**
[figure not shown]
Television app development process.

### Data Collection

During the study, 3 different collection points are planned: baseline assessment, end of intervention assessment (at 3 months after the beginning of the intervention) and follow-up assessment (at 6 months after the beginning of the intervention). Clinical assessments will be performed by a multidisciplinary team (medical doctor, nurse, nutritionist, and physiotherapist) at primary care centers involved in this study. Structured evaluations will be conducted with a computer-assisted personal interview (CAPI) system. Each assessment will start with the medical doctor evaluation, followed by the nutritionist, physiotherapist, and nurse evaluation. As explained above, before the baseline assessment, the medical doctor will obtain the informed consent and check the eligibility of the participant.

During the baseline assessment, the following sociodemographic data and socioeconomic profile variables will be recorded: age, sex, ethnicity, education, marital status, measures of wealth (used to generate income quintiles), and household income. Also, medical history and physical examination will be performed by the medical doctor. In addition, the following data will be collected: health care resource consumption (number and type of outpatient clinic visits, hospitalizations, home care assistance, and other needs for health care services in the previous 12 months), health-related quality of life (European Quality of Life questionnaire with five dimensions and three levels [EQ-5D-3L] and the Functional Assessment of Chronic Illness Therapy–Fatigue [FACIT-F]), lifestyle behaviors (alcohol and coffee consumption, smoking habits, and regular physical activity), physical function (Health Assessment Questionnaire [HAQ]), anxiety and depression symptoms (Hospital Anxiety and Depression Scale [HADS]), self-reported chronic diseases (high cholesterol level, high blood pressure, allergy, gastrointestinal disease, mental disease, cardiac disease, thyroid and parathyroid disease, urolithiasis, pulmonary disease, hyperuricemia, malignancy, neurologic disease, and rheumatic and musculoskeletal diseases), and information regarding pharmacological and nonpharmacological therapies.

A nutrition and physiotherapy assessment will be performed at baseline and end of intervention assessment (at 3 months). The nutritionist will collect data regarding food insecurity (Household Food Insecurity Scale [HFIS] adapted from the US Department of Agriculture Household Food Security Survey Module [21]), dietary habits (2-day 24-hour diet recall, Prevención con Dieta Mediterránea [PREDIMED] index [31], and food frequency questions), anthropometric data (height, weight, and waist circumference), body composition data obtained by bioimpedance (fat mass, fat-free mass, total body water), attitudes and barriers on diet, food expenses, and other resources for food. Regarding the dietary habits assessment, a second 24-hour diet recall will be performed by phone call interview performed within 1 week.

Physiotherapy assessment will be conducted aiming at collect data regarding physical activity (Elderly Mobility Scale [EMS] [32] and International Physical Activity Questionnaire [IPAQ]) and muscle strength (hand grip, knee extension, and hip flexion by using a dynamometer). The assessment scales used in the study are all Portuguese-validated versions, and the average time for the evaluation will be 90 minutes.

The nurse will perform a structured questionnaire in order to capture baseline knowledge on healthy lifestyles. This questionnaire will be repeated during the 3-month and 6-month follow-up assessments.

Blood samples will also be collected in order to obtain data regarding the nutritional status and serological biomarkers of cardiovascular risk (albumin and prealbumin levels, insulin resistance, cholesterol levels, hemoglobin A_1c_, adipocytokines, high sensitivity C-reactive protein, interleukin 1, interleukin 6, and tumor necrosis factor).

At the 6-month follow-up time point, the assessment will be telephonically performed with the assistance of a CATI system (an in-house software platform) by a team of research assistants. These data will be collected in a standardized form; database access is protected by unique username and password for each research team member. In this telephone interview, we will collect data regarding food insecurity (HFIS [21]), dietary habits (2-day 24-hour diet recall, PREDIMED index [31], health-related quality of life and health status (E-5D-3L and FACIT-F), physical activity (IPAQ), consumption of health care resources (inpatient admissions and outpatient appointments), functional disability (HAQ), anxiety and depression symptoms (HADS), and lifestyle behaviors (see Multimedia Appendix 1 for a schedule of all collected data). Finally, the intervention group data regarding the adherence to the program will be monitored using the TV interactive data.

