### Outcome Measures

The primary outcome assessed will be the changes in participant food insecurity score (evaluated by the HFIS) from baseline to 3 months. Secondary outcomes at 3 months will be changes in dietary habits (evaluated by 2-day 24-hour recall, PREDIMED index [31], and food frequency questions), changes in indicators of nutritional status (body mass index [BMI] and albumin and prealbumin levels), changes in muscle strength improvement (evaluated by dynamometer), changes in quality of life (EQ-5D-3L) [33], changes in fatigue scale (FACIT-F) [34], changes in serological markers of cardiovascular risk (insulin resistance, cholesterol levels, hemoglobin A_1c_, high sensitivity C-reactive protein, adipocytokines, interleukin 1, interleukin 6, and tumor necrosis factor), changes in physical activity (EMS [32] and IPAQ [35]); changes in body composition balance evaluated by bioimpedance, changes in inpatient admissions and outpatient appointments, changes in falls, and changes in knowledge regarding healthy lifestyle.

The secondary outcomes at 6 months will be changes in participant food insecurity score, changes in dietary habits (2-day 24-hour recall, PREDIMED index [31], and food frequency questions), changes in quality of life (EQ-5D-3L) [33], changes in fatigue scale (FACIT-F), changes in physical activity (IPAQ) [35], changes in inpatient admissions and outpatient appointments, changes in falls, and changes in knowledge regarding healthy lifestyle.

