### Data Analysis

Analysis will be performed with Stata software (StataCorp LLC). Continuous variables will be reported as mean and standard deviation (or in case of nonnormal distribution as median and interquartile range). Categorical variables will be displayed as frequencies or proportions. The association between food security status, dietary data, and health outcomes will be assessed through chi-square analysis of baseline data.

To assess the effect of the interventional program on food security, dietary intake, nutritional status and body composition, quality of life, muscle strength, fatigue scale, physical activity habits, and serological markers of cardiovascular risk, 2-tailed *t* tests will be used to compare the amount of change within each group (baseline, end of study [at 3 months] and follow-up [at 6 months]). Independent sample *t* tests will be used to compare the intervention group and control group on the same outcomes.

Dietary intake assessed with 2-day 24-hour recall will be analyzed according to the recommended number of servings from each food group of the Portuguese Food Wheel [37]. Intakes of micronutrients that tend to be low in vulnerable population groups (iron, calcium, folate, and vitamins A, C, and D) will be also analyzed. The percentage of individuals meeting the Estimated Average Requirement or Adequate Intake for iron, calcium, folate, and vitamins A, C, and D will be calculated [38]. Food Processor Nutrition Analysis software (ESHA Research) will be used to estimate the intakes of energy, macro-, and micronutrients.

The association between each outcome and the candidate covariables will be performed using generalized models. We will use multivariate logistic and linear (according to the outcome) regression models. The candidate covariates will be first analyzed by univariate regression. Covariates will enter the multivariate models if their *P* value is less than .25 in univariate analysis or considered clinically relevant in this setting. The selection of covariates will be stepwise by backward selection, according to the level of significance (<.05). Multilevel analysis and sensitive analysis will be performed when appropriate.

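### Within-arm change to 6 months cannot be separated from the switch to telephone interviewing, yet the Data Analysis section tests it as a programme effect

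*Protocol article*

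**What the plan says.** **Baseline and 3 months.** The Data Collection section places these assessments in the clinic: "Clinical assessments will be performed by a multidisciplinary team (medical doctor, nurse, nutritionist, and physiotherapist) at primary care centers involved in this study". The mode is personal interview: "Structured evaluations will be conducted with a computer-assisted personal interview (CAPI) system". HFIS and diet fall to the nutritionist and IPAQ to the physiotherapist: "A nutrition and physiotherapy assessment will be performed at baseline and end of intervention assessment (at 3 months"). Diet is already mixed-mode at these visits, because "a second 24-hour diet recall will be performed by phone call interview performed within 1 week".

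**6 months.** "At the 6-month follow-up time point, the assessment will be telephonically performed with the assistance of a CATI system", carried out "by a team of research assistants". The telephone interview covers HFIS, the 2-day recall, PREDIMED, EQ-5D-3L, FACIT-F and IPAQ, among others.

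**Outcomes.** The primary outcome comes before the switch: "The primary outcome assessed will be the changes in participant food insecurity score (evaluated by the HFIS) from baseline to 3 months". Changes to 6 months in HFIS, diet, quality of life, fatigue and physical activity are secondary.

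**Analysis.** The Data Analysis section assesses the programme with two-tailed t tests to "compare the amount of change within each group (baseline, end of study [at 3 months] and follow-up [at 6 months"]). The next sentence plans independent-samples t tests between the arms on the same outcomes.

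**The concern.** Every participant moves from in-person to telephone interview, and from clinical staff to research assistants, at the same time and after the 3-month programme has ended. Within an arm, time and mode are therefore completely aliased. People may report food insecurity, diet or activity differently to a research assistant on the telephone than to a nutritionist in the health centre. If so, the within-arm mean moves even when nothing real has changed.

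The Data Analysis section presents the within-group tests as a way to assess the programme's effect. A significant rise or fall in the intervention arm at 6 months could then be reported as relapse or continued benefit when it reflects how the question was asked. This applies to change from baseline to 6 months and from 3 to 6 months.

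**Working it through.** **Inputs from the Sample Size section:** SD of change 1.5; target difference 0.5; 141 per arm; power 0.80; alpha .05. The Data Analysis section gives two-tailed tests.

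**1. The plan's own figure.** n per arm = 2 × (1.96 + 0.842)² × 1.5² / 0.5² ≈ 141.3. This rounds up to 142, against the stated 141. Power at 141 per arm is 0.80 (0.797 by the exact t calculation). The stated sample size reproduces.

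**2. Precision of a within-arm mean change.** SE = 1.5 / √141 = 0.126. The smallest mean change reaching p < .05 is t(0.975; 140) × 0.126 = 0.25 points, half the target effect. A mean shift of 0.25 needs only one participant in four to score one point differently.

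**3. Effect of a pure mode shift.** Let d be a shift common to both arms, with no true change. The documents give no value for d, so the range is assumed. The within-arm rejection probability is approximately Φ(d/SE − 1.96) + Φ(−d/SE − 1.96); the table uses the exact t version. In the between-arm contrast d cancels: (true change + d) − (true change + d) = 0.

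| Assumed shift d (HFIS points) | Within-arm test significant | Between-arm test significant |
|---|---|---|
| 0.1 | 12% | 5% |
| 0.25 | 50% | 5% |
| 0.5 | 98% | 5% |

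A simulation of 20,000 trials agrees. At shifts of 0.25 and 0.5 the within-arm rejection was 0.507 and 0.975; the between-arm rejection was 0.049 and 0.050, with mean bias about zero.

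**4. Sensitivity to the SD.** For the same three shifts, an SD of 1.0 gives 22%, 84% and 100%. An SD of 2.0 gives 9%, 31% and 84%.

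**5. When the between-arm test would be affected.** Only if the mode effect differs by arm. For assumed differences of 0.1, 0.2 and 0.25 points, rejection would be about 9%, 20% and 29%. Nothing in the article indicates such a difference.

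**The case against.** The strongest reply is that the protocol already contains the right test. The sentence after the within-group tests plans the between-arm comparison on the same outcomes. Both randomized arms switch mode together, so a common shift cancels. This stands. A reader might infer that the whole 6-month assessment, or any conclusion on persistence, is confounded with mode; the documents do not support that.

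Other parts of the reply also stand:

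- **Primary outcome.** HFIS change to 3 months is measured in the clinic at both ends, so neither it nor the sample size is affected.
- **No mode adjustment.** A reader might fault the plan for omitting one. Within an arm mode and time are perfectly collinear, so no model could supply it.
- **Diet.** The second recall is by telephone throughout, so diet moves from mixed mode to telephone rather than from one mode to the other.
- **Persistence.** The article defines no separate persistence or relapse endpoint. How a within-arm result would be reported is a prediction.
- **Magnitude.** The figures depend on an assumed shift.

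What does not stand is the suggestion that nothing is left. The within-group tests through 6 months are stated in the article, under the purpose of assessing the programme's effect. They are not a detail left to an analysis plan. Blinding of follow-up assessors does not help either, because the shift at issue is common to both arms.

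**Conclusion.** The point holds for within-arm inference at 6 months on interview-based secondary outcomes: HFIS, PREDIMED, EQ-5D-3L, FACIT-F, IPAQ and, in part, the 24-hour recall. For these, change to 6 months from either earlier time point is inseparable from the change of mode and interviewer, and the plan tests it as an effect of the programme.

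The false-positive probability of about 12% to 98% is an illustration, not an estimate. It rests on an assumed shift of 0.1 to 0.5 points and no true change. It also carries the plan's SD of 1.5, set for change to the end of study (3 months in the Data Analysis section), over to intervals ending at 6 months, with all 141 per arm retained. The article does not show that a mode effect exists. The aliasing is a fact of the design whatever its size. The issue is moderate, confined to secondary inference, and worth correcting because correction is nearly free.

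**What to change.** Amend the Data Analysis section as follows:

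- Rest conclusions about effect at 6 months, and about persistence, only on the between-arm difference in change at 6 months, set beside the same difference at 3 months.
- For items that switch mode, report within-arm change to 6 months descriptively, without significance tests.
- State the change of mode and interviewers at 6 months as a limitation.

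An optional sensitivity analysis for diet could compare the telephone recall already taken at baseline and 3 months with the telephone recalls at 6 months. It is less precise, because it uses only one recall day at each earlier time point.

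The cost is wording only, plus the loss of within-arm tests that cannot be interpreted. Visits, data collection and sample size do not change.
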